## Discussion

The primary objective of this non-randomized prospective observational study is to evaluate the effects of subcutaneous injectable depot buprenorphine on the quality of life of opioid dependent patients in routine OST care in Germany. Together with the secondary objectives, the study aims to provide an overall assessment toward addiction recovery among OST patients treated with subcutaneous injectable depot buprenorphine. The main strength of the study and added value to previous research is this holistic approach in the study objectives and respective variables. By combining clinical OST routine care data with patient-reported outcomes, and comparing depot buprenorphine against other OST medications, this study will help to estimate the impact of depot buprenorphine on quality of life and recovery under real-world conditions.

At the same time, this naturalistic design bears some limitations, most importantly the lack of randomization. OST patients with the decision to switch to subcutaneous injectable depot buprenorphine might differ from other OST patients in several aspects, such as disease severity and psychosocial functioning. To minimize potential selection biases, a matched pair control group design was selected to ensure that OST patients in the depot buprenorphine group will not significantly differ from those in the control group with respect to gender, duration of OST, take-home prescription and psychosocial functioning (GAF-percentiles). A second advantage of the matched-pair design is that OST units in Germany are organized in different primary care settings and vary in the provision of health and psycho-social care as well as in the number of patients per unit. As the number of OST patients in the depot buprenorphine group per unit might be low, a pairwise matching of control patients from the same OST unit was selected instead of a cluster-randomized controlled trial design with a fixed number of patients per cluster.

Another limitation consists in the heterogeneity of the TAU group, especially in terms of OST medication. A comparison between depot buprenorphine and sublingual buprenorphine only would help to identify effects of the application form. However, as (levo-)methadone is still the most frequently used OST agent in Germany (BfArM 2020) (2), we preferred not to exclude this large patient group and adhere to our naturalistic and observational approach.

One further limitation is that the study duration for each patient (12 months) only allows to measure recovery processes over a short period of time. As addiction recovery is a lifelong process, the study therefore does not provide empirical data about the processes of recovery over a longer period of time.

Altogether, this study will provide new insights in the addiction recovery processes of opioid-dependent patients in OST treated with depot buprenorphine over time, including comparisons with patients treated with other OST medications.

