### Study Design

The study objectives will be evaluated in a non-randomized prospective non-interventional observational study with control group design (treatment-as-usual, TAU). All OST patients with TAU (i.e., treated with any registered OST medication, but not with injectable depot buprenorphine (e.g., racemic methadone, levomethadone, sublingual buprenorphine or slow release oral morphine) can take part in the control group. In order to avoid a selection bias and to ensure an overall comparability of the patient groups (injectable depot buprenorphine vs. TAU), one suitable patient from the OST unit will be pairwise matched to each recruited depot buprenorphine patient. Matching variables are gender (male /female), duration of OST (years), take-home prescription (yes /no) and patients' functioning measured by the global assessment of functioning scale (according to percentiles measured by the Global Assessment of Functioning Scale, GAF). Prior to matching, all patients from each participating OST unit will be screened for these four criteria based on an anonymized list of patients. After inclusion of a depot buprenorphine patient, a respective OST patient who is not willing to switch to depot treatment will be asked to participate as control group patient. An overview of the study design is provided in Figure 1.

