### Variables

The following variables will be collected at baseline (t_0_) and follow-ups [month 1 (t_1_), 3 (t_2_), 6 (t_3_), 12 (t_4_)]:

- **Sociodemographic data** including gender, age, current housing, work, family status/partnership.- **Health data** will be collected using the Opiate Treatment Index-Health Symptom Scale (OTI-HSS), a symptom checklist to assess the patient's current health status with regard to medical problems that opioid users often develop (e.g., injection-related problems, cardio/respiratory problems, musculoskeletal problems, neurological problems, gastro-intestinal problems (21, 22).- **OST data** (medication, doses) routinely collected by the OST practice/clinic.- **Quality of life** will be measured by the OSTQOL, a disease-specific instrument for measuring quality of life among patients in OST (20). First analyses in developmental processes of the OSTQOL showed acceptable internal consistencies of all subscales (personal development, psychological stress, social contacts, material well-being, OST and discrimination), with Cronbach's alpha between 0.75 and 0.88, as well as a good convergent and discriminant validity of the instrument (20).- The **patient acceptance** of injectable depot buprenorphine will be measured along the four key dimensions of the Treatment Satisfaction Questionnaire for Medication (TSQM-14) (effectiveness; side effects; convenience and global satisfaction).- The **Client Satisfaction Questionnaire (CSQ-8)** will be used to measure the patients' satisfaction with the overall OST care. The short 8-item instrument has been frequently used in substance use research including OST (23, 24) and has shown a high internal consistency and concurrent validity (25).- Parts (heroin craving, acceptance of the OST medication) of the **Opiate Dosage Adequacy Scale (ODAS)** will be used to measure the adequacy of opioid doses among the patients in the depot buprenorphine group. The ODAS consists of six domains (heroin consumption, narcotic blockade, mental and somatic opiate withdrawal syndrome, craving for heroin, and OST overdosing) including items which can be answered by the patient. Scores range between 1 (worst) and 5 (best). Cut-off scores of 3 or less in any ODAS domain will be regarded as not adequately dosed. The ODAS was found to have a good validity and reliability to measure and assess buprenorphine dose adequacy in the context of OST (26).- Data on **substance use** will be collected on the basis of patient self-report using the drug and alcohol use domain of the European Addiction Severity Index (EuropASI) (27). The data on substance use will be complemented by urine samples collected within routine OST care. The urine samples will be tested for heroin, non-prescribed substitutes, cocaine/crack, amphetamine, cannabis and benzodiazepine use.- **The psychological distress** among the patients will be measured by the Brief-Symptom-Inventory 18 (BSI-18), (28). The questionnaire comprises 18 items on physical and psychological symptoms, rated on a 5-point Likert scale (0 = not at all; 4 = very much) with regard to the last 7 days, and yields 3 sub-scores for depression, anxiety, and somatization, as well as an overall Global Severity Index (GSI).- **Social participation** will be measured by a self-developed short questionnaire including questions on the number and kind of social activities (e.g., recreational or physical activities, activities with friends, family) within the last week.- Data to calculate the **retention in treatment** will be collected by the date of ending OST or changing OST medication. The dates will be collected retrospectively by the treatment staff at any follow-up timepoint of the study. Retention in treatment will be calculated by dividing the number of patients in each study arm at each follow-up visit by the total number of patients in each study arm at baseline.- Quality-adjusted life years (QALYs) will be used for the **cost-effectiveness analysis**. Respective data will be collected with the EuroQOL five dimensions questionnaire (EQ-5D) (29).

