#### Secondary Outcome Analyses

Secondary data analyses will be carried out in accordance with the scale levels of the variables or scores and indices (drug consumption, somatic or mental health symptoms, quality of life, withdrawal symptoms, craving, treatment satisfaction) and along the expected relationships between individual variables, e.g., in the context of bivariate or multivariate analyses. Comparisons between depot patients and matched control group will be done by a mixed model approach with baseline OSTQOL score and the (pairwise) cluster term as covariates and will include all follow-up measurement points, such as month 3 and month 6 (see Table 2). Retention rates will be analyzed using descriptive statistics. For group comparisons, Chi^2^-tests (percentages) as well as Kaplan-Meier survival methods and Log-Rank Tests will be used. The significance level will be defined at *p* < 5%.

**Table 2 T2:** Overview of outcome domains, instruments and measurement.

**Outcome domain**	**Instrument**	**t_**0**_**	**t_**1**_**	**t_**2**_**	**t_**3**_**	**t_**4**_**
Quality of life	OSTQOL	x		x	x	x
Acceptance	TSQM-14	x	x	x	x	x
Patient satisfaction with	CSQ-8	x	x	x	x	x
OST care						
Dosage adequacy	ODAS	x	x	x	x	x
Substance use	EuropASI, Urine samples	x	x	x	x	x
Psychological distress	BSI-18	x			x	x
Social participation	Self-constructed questionnaire	x			x	x
Retention	CRF		x	x	x	x
Cost-effectiveness	EQ-5D	x			x	x
Health	OTI-HSS	x			x	x
Adverse events	AE, SAE, ADR	If necessary				

*t_0_, baseline; t_1_, month 1; t_2_, month 3, t_3_, month 6 and t_4_, month 12; OSTQOL, Opioid Substitution Treatment Quality of Life scale; TSQM-14, Treatment Satisfaction Questionnaire for Medication; CSQ-8, Client Satisfaction Questionnaire; ODAS, Opiate Dosage Adequacy Scale; EuropASI, European Addiction Severity Index; BSI-18, Brief Symptom Inventory 18; CRF = Case-Report Form; EQ-5D, EuroQOL five dimensions questionnaire; OTI-HSS, Opiate Treatment Index-Health Symptom Scale; AE, adverse event; SAE, serious adverse event; ADR, adverse drug reaction*.

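### Disease severity is named as a possible difference between depot and control patients, but it is neither matched on nor a stated covariate in the secondary group comparisons, although severity measures are taken at baseline

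*Protocol article*

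**What the plan says.** In the Discussion, the limitations paragraph gives two examples of how patients who switch to depot buprenorphine "might differ from other OST patients in several aspects, such as disease severity and psychosocial functioning". It then presents the matched-pair design as the way to reduce this selection bias and says the groups will be comparable "with respect to gender, duration of OST, take-home prescription and psychosocial functioning (GAF-percentiles").

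The Study Design section gives the same list: "Matching variables are gender (male /female), duration of OST (years), take-home prescription (yes /no) and patients' functioning measured by the global assessment of functioning scale". Controls come from the same OST unit.

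Under Secondary Outcome Analyses, depot and control patients are compared by a "mixed model approach with baseline OSTQOL score and the (pairwise) cluster term as covariates". The Abstract names the same two terms. The section also mentions secondary analyses in general, "e.g., in the context of bivariate or multivariate analyses", without naming any covariate. Retention is compared by Chi-square and log-rank tests.

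The Variables section and Table 2 place several severity-related measures at t0: the "drug and alcohol use domain of the European Addiction Severity Index (EuropASI") with urine samples, the OTI-HSS symptom checklist, and the BSI-18 with its global index. Age, housing and work are also recorded at baseline.

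The Abstract states that the matching permits conclusions about the effects of the different medications.

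**The concern.** In a non-randomised comparison, the adjustment set decides how far a group difference can be read as a treatment effect. The plan names two possible differences between the groups, and the remedy it describes covers only the second directly.

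Other parts of the design make a severity difference plausible. Patients not eligible for depot treatment under the SmPC are barred from the depot arm but may serve as controls (Selection and Treatment of Participants). Controls are patients unwilling to switch (Study Design). The Treatment section expects greater willingness among patients who had problems with their previous medication.

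The secondary endpoints compared between groups include substance use, psychological distress, social participation and cost-effectiveness, all plausibly related to severity. If severity differs within pairs and also predicts the month-12 outcome, part of the estimated difference reflects who chose depot treatment rather than the medication. The data that would reduce this are already collected.

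**Working it through.** **1. What is covered**

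| Characteristic | Matched | Stated covariate | Measured at t0 |
|---|---|---|---|
| Psychosocial functioning | yes (GAF percentiles) | no | yes |
| Gender, OST duration, take-home status, OST unit | yes | through the pair term only | yes |
| Quality of life | no | yes (baseline OSTQOL) | yes |
| Substance use | no | no | yes (EuropASI, urine) |
| Somatic health | no | no | yes (OTI-HSS) |
| Psychological distress | no | no | yes (BSI-18) |
| Age | no | no | yes |

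Substance use and BSI-18 are group-comparison endpoints, so they must be measured in both arms. The article restricts OTI-HSS to neither arm.

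**2. The plan's own figures (Sample Size Calculation)**

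- Paired test, d = 0.25, two-sided 5%, power 80%: the normal approximation gives (1.960 + 0.842)² / 0.25² = 125.6. The noncentral t gives 127.5, so 128 as stated.
- Drop-out of 40%: 128 / 0.60 = 213.3, consistent with the stated 213.
- Group comparison with 128 per arm: SE = √(2/128) = 0.125 SD. At d = 0.35 the power is 0.7996, and the t-based detectable effect at 80% power is 0.352. The stated d = 0.35 reproduces.

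These figures are sound. They give the scale for step 3.

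**3. Illustration of a possible bias**

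The article gives neither a severity imbalance nor a severity-outcome association, so both inputs are assumptions:

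- gap: standardised severity difference between arms that remains given pair and baseline OSTQOL, 0.2-0.3 SD;
- slope: change in month-12 OSTQOL per SD of severity, given the same terms, 0.2-0.3.

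Bias = gap × slope. Two-sided rejection rate under no true effect = Φ(−1.96 + bias/SE) + Φ(−1.96 − bias/SE). It is shown for 128 per arm with SE = 0.125 (no gain from baseline adjustment) and with SE = 0.125 × √(1 − 0.6²) = 0.10 (assumed baseline correlation 0.6).

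| Gap | Slope | Bias (SD) | Share of 0.35 | Rejection, SE 0.125 | Rejection, SE 0.10 |
|---|---|---|---|---|---|
| 0.2 | 0.2 | 0.04 | 11% | 6.2% | 6.9% |
| 0.2 | 0.3 | 0.06 | 17% | 7.7% | 9.2% |
| 0.3 | 0.2 | 0.06 | 17% | 7.7% | 9.2% |
| 0.3 | 0.3 | 0.09 | 26% | 11.1% | 14.7% |

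A wider assumed range (gap 0.2-0.5, slope 0.1-0.4) gives a bias of 0.02-0.20 SD, which is 6-57% of 0.35, and rejection rates of 5.3-36% at SE 0.125. With all 213 per arm and no baseline gain (SE = √(2/213) = 0.097), the 0.04 and 0.09 cases give 7.0% and 15.3%. More patients do not shrink the bias; they only make it easier to declare significant. The SEs ignore the pair term and the repeated measures, so the rejection rates are rougher than the bias figures.

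**4. Direction**

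The sign is not fixed by the document. If more severely ill patients move to depot treatment and severity lowers OSTQOL, the bias runs against depot. If patients ineligible for depot treatment are more severely ill and accumulate among controls, it runs in favour of depot.

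**The case against.** Four arguments deserve weight.

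*Severity is partly handled.* GAF, take-home status, OST duration and the shared unit are plausible markers of clinical stability. Baseline OSTQOL includes subscales on psychological stress, social contacts and material well-being, which overlap with BSI-18, housing and work. This stands: the remaining gap is mainly substance use, somatic health and age. It is narrowed, not closed.

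*The full analysis plan may add covariates.* The article does not say its list is complete, and it mentions multivariate analyses in general terms. But it states the adjustment set for the group comparison in both the Abstract and the analysis section, and it names no severity term in either. That is a stated choice that can be improved, not a detail left open. One might infer that the plan rules out further adjustment; the text does not say so.

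*The source is hedged.* A reader might infer that severity is an expected or known confounder. The Discussion says only that patients might differ and gives severity as an example; no imbalance or outcome association is reported.

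*The limitation is disclosed.* The Discussion calls the lack of randomisation the most important limitation and speaks of minimising bias. This stands, but the Abstract's sentence about medication effects is not similarly qualified.

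**Conclusion.** The point holds for the secondary depot-versus-control comparisons. A characteristic that the plan itself raises as a possible group difference is in neither the matching set nor the stated covariates, although direct measures of it are taken at baseline. The result is residual confounding that could be reduced at little cost.

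The illustrative bias of 0.04-0.09 SD (11-26% of d = 0.35) depends wholly on the assumed gap and slope. The document supports neither a particular size nor a direction, so the rejection rates above must not be read as the study's false-positive rate.

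A reader might also infer that the main result is compromised. It is not affected by this point: under Primary Outcome Measure, the primary endpoint is the change within the depot group and involves no comparison with controls. Adjustment would remove only the part of severity that the baseline scores capture; unmeasured differences would remain.

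**What to change.** - In the depot-versus-control mixed models, prespecify a short set of t0 covariates: age, EuropASI substance use, OTI-HSS and BSI-18 GSI. One propensity score built from them is an alternative.
- Report standardised baseline differences by arm for this set and for the matching variables.
- Keep the model with baseline OSTQOL and the pair term as a sensitivity analysis, so that readers can see what the adjustment changes.
- For retention, keep the Chi-square and log-rank tests, which take no covariates, and add an adjusted analysis beside them, such as Cox or logistic regression.
- Limit the Abstract's sentence: matching and adjustment reduce measured confounding, and conclusions about medication effects depend on the absence of important unmeasured differences.

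The cost is analysis wording and a few degrees of freedom: four covariates for about 2 × 128 = 256 patients with month-12 data. No new data are needed. The one practical drawback is that occasional missing baseline covariates need a prespecified rule, so that pairs are not broken by dropping incomplete patients.

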## Ethics and Dissemination

### Ethical Considerations

In accordance with § 67 of the AMG (Arzneimittelgesetz, Medicinal Products Act) the study has been announced at the Federal Institute for Drugs and Medical Devices (Bundesinstitut für Arzneimittel und Medizinprodukte, BfArM), the National Association of Statutory Health Insurance Physicians (Kassenärztliche Bundesvereinigung, KBV), the National Association of Statutory Health Insurance Funds and the Private Health Insurance Association.

The study and its documents (including study protocol, case-report-form, patient information, patient consent) has been approved by the independent ethics committee (IEC) of the Hamburg Chamber of Physicians (Ärztekammer Hamburg, reference number: PV7078; September 19^th^, 2019). Upon receipt of the primary ethical vote, secondary votes will be applied for OST units outside of Hamburg.

The study will be conducted in accordance with the current version of the Declaration of Helsinki (adopted by the 18th General Assembly of the World Medical Association in Helsinki, Finland, in June 1964 and supplemented by the 29th General Assembly in Tokyo, Japan, in October 1975, 35th General Assembly in Venice, Italy, October 1983, 41st General Assembly in Hong Kong in September 1989, 48th General Assembly in Somerset West, Republic of South Africa, October 1996 and the 52nd General Assembly in Edinburgh, Scotland, in October 2000, and the clarifications, made by the 53rd General Assembly of the World Medical Association in Washington, USA in October 2002 and the 55th General Assembly in Tokyo, Japan, in October 2004, as well as the revisions by the 59th WMA General Assembly in Seoul, Korea, in October 2008 and the 64th WMA General Assembly Fortaleza, Brazil, in October 2013).

#### Patient Information and Informed Consent

To be eligible for study participation, all patients have to provide their written consent after having been informed in detail about the study objectives, nature, extent and risks. The date of the written consent has to be noted. Prior to consent, no investigations, surveys or other measures associated with the study will be conducted.

#### Data Protection

Throughout the documentation and evaluation phases, all patients will be solely identified by an encoding number assigned to them for the purpose of this study. Patients will be informed that all findings and data collected during the study are stored electronically and treated with strict confidence.

#### Liability and Insurance

As non-interventional and observational, the study is not subject of §§ 40 and 41 of the German Federal AMG and therefore does not require a patient insurance. Participation in the study will not expose the patients to any particular risk.

#### Quality Assurance

As part of the quality assurance, the OST unit staff will be briefed on the study objectives and the study documentation. On-site monitoring will be conducted. Within the monitoring, trained employees of the Center for Interdisciplinary Addiction Research of Hamburg University (ZIS) will check the collected data for completeness and plausibility. Missing data will be supplemented by the study centers on-site. The study has been registered at the German Register of Clinical Trials (DRKS, ID: DRKS00020797).

#### Handling With AEs and ADRs

The occurrence of adverse events will be documented in pseudonymized form by medical OST staff in the “Documentation sheet on adverse events.” The event is classified according to intensity, frequency, outcome, causal link to the substitution medication and time.

Serious adverse events (e.g., life-threatening overdose or possible other adverse drug reactions) will be documented in the “Report on adverse drug reactions (ADRs),” which has to be sent to the study management (ZIS) within 24 h. Incoming ADR messages will immediately be forwarded to the Ethics Committee. All adverse events and adverse drug reactions will be reported in the final report.

#### Dissemination

The study outcomes will be disseminated by presentations at scientific conferences and in peer-reviewed, open-access publications.

